### Participant consent

Interested women who cannot read will be read aloud the information sheet. If unable to write, participants will record a thumb print, signed by a literate witness (a high school-educated assistant) after confirming that the information sheet has been read aloud correctly; otherwise, participants will provide written informed consent. Study documents will be kept in the locked research office but will be accessible to women at their request. The information sheet includes details of how participants can access compensation, if required.

### Participant reimbursement

All participants will be reimbursed for their time attending research interviews in addition to transport costs and any additional expenses incurred. Participants will be reimbursed for transport costs to attend PST or PST-IPV sessions but will not be compensated for their time during these sessions. This is to determine the acceptability of psychological intervention sessions to women and enable calculation of drop-out rates. A fund will be available to assist participants disclosing IPV who wish to access support services (for example. to facilitate transport to a government social support office or police station).

### Masking

Given qualitative differences between PST and PST-IPV, clinicians delivering the intervention cannot be masked to participant allocation. To avoid contamination, PST-IPV, standard PST and enhanced usual care will be delivered by different practitioners who have either attended a PST-IPV or a standard PST training course, or received basic training to provide enhanced usual care. Post-intervention outcome assessments will be conducted by trained, independent assessors (working in separate offices from practitioners delivering interventions and not travelling together) masked to intervention allocation, with a minimum post-high school diploma level of education. Independent assessors will document any incidents of unmasking. Data analysts will also be masked to intervention allocation.

### Intervention arms

Participants randomised to PST-IPV or standard PST will attend four intervention contacts within a maximum of 8 weeks. Where birth occurs before the end of treatment, the feasibility of continuing PST-IPV or standard PST post-natally will also be assessed.

Both manualised interventions will be delivered by trained health workers, such as nurses and midwives, supervised by Psychology Masters-level qualified research staff, with access to a project mental health professional for clinical concerns. Responses to concerns and risk incidents will follow standard operating procedures (SOPs). Government-employed health workers trained to deliver the interventions will be paid for their time.

Both PST-IPV and standard PST intervention arms follow the same structure of four sessions, based on the model successfully employed in South Africa and adapted for this rural Ethiopian setting [27, 66]. Session 1 focuses on basic psychoeducation, introduction to PST, identifying the most important things in the woman’s life and categorising problems into three groups. Session 2 focuses on revising session 1, coping strategies for ‘group A’ problems (which are upsetting but do not influence the most important things in the woman’s life) and the six-step problem solving method for ‘group C’ problems (which are important and can be solved). Session 3 focuses on revising session 2, coping strategies for ‘group B’ problems (which are important but cannot be solved) and psychoeducation about the phases of coping with bereavement and loss. Session 4 focuses on revising session 3, using problem solving skills in everyday life and reviewing how the coping strategies worked in practice. All sessions involve assigning and reviewing take-home activities.

PST-IPV content and materials are adapted to address the needs and experiences of women affected by IPV, whilst standard PST content and materials are generic. Adaptations for women experiencing IPV include training staff using content and materials from the new WHO curriculum on caring for women subjected to violence [67], attention to safety and sensitivity where women list IPV-related problems during sessions (including training with worked examples of problem solving focused on IPV), and adaptation of PST case studies to reflect common problems associated with IPV.

Participants randomised to PST-IPV or standard PST will attend a total of six contacts: one baseline pre-intervention research assessment, four intervention contacts and a follow-up research assessment contact 9 weeks after recruitment. The feasibility of follow-up 9 weeks after recruitment will be assessed and may change, depending on gestation of pregnancy at the time of enrolment.

### Enhanced usual care arm

One-third of participants will be randomised to information only about sources of support (enhanced usual care; see Supplementary file 2). They will attend two contacts: one pre-intervention assessment at which they are provided with information about relevant sources of support, and one follow-up assessment 9 weeks later.

In our meta-analysis we found that randomisation of control group participants with depression, anxiety, PTSD or psychological distress symptoms and IPV exposure to waiting list, treatment as usual, or enhanced usual care arms is widespread [21]. This, coupled with the lack of any standard intervention provision for perinatal depression and/or IPV in rural Ethiopia and the provision of safeguards in the study design, justify the use of a control arm, which comprises enhanced usual care (provision of information about sources of support).

### Measurement: participants

Women will be assessed at baseline and then 9 weeks later in a private room of the health care facility at a time convenient to them (Fig. 2). During these assessments, fully structured measures will be administered to consenting participants in an interview format. The time taken to complete planned questionnaires will be tested prior to commencing the study. Where administration of study measures takes longer than 1 h per session or is experienced by research staff or participants as unduly burdensome, instruments will be removed from the assessment questionnaire. This information will contribute to the study’s process evaluation.

**Fig. 2 Fig2:**
[figure not shown]
Schedule of participant enrolment, interventions and assessments. CSRI client service receipt inventory, GAD-7 Generalised Anxiety Disorder 7 scale, IPV intimate partner violence, MINI Mini-International Neuropsychiatric Interview, OSSS-3 Oslo Social Support Scale 3, PCL-5 post-traumatic stress disorder checklist for Diagnostic and Statistical Manual version 5, PHQ-9 Nine-item Patient Health Questionnaire, PST problem solving therapy, PTSD post-traumatic stress disorder, WHO World Health Organization, WHODAS World Health Organization Disability Assessment Schedule

#### Primary participant outcome

At baseline and the independent, masked, 9-week follow-up interview, depression symptoms will be measured using the Amharic-translated PHQ-9 [59], a nine-item questionnaire asking about the presence of depressive symptoms in the preceding 2 weeks. Each item is rated according to persistence of the symptom (0 = not at all, 1 = several days, 2 = more than half of the days, 3 = nearly every day). PHQ-9 scores pre- and post-participation will be compared to calculate the mean difference in depression symptom reduction in PST-IPV, standard PST and enhanced usual care arms. Proportions of participants showing a treatment response, defined as a 50% reduction in PHQ-9 score, will also be calculated, although this feasibility trial will not be powered to detect treatment efficacy.

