### Participant sample size

As a feasibility trial, this study is not powered to detect intervention efficacy, but rather to estimate feasibility parameters to inform a future RCT, and test intervention and research protocols. With a total sample size of 75 (25 participants randomised to PST-IPV, 25 to PST and 25 to enhanced usual care), a drop-out rate of 30% can be estimated to within a 95% confidence interval of ±3%. To estimate the standard deviation of the primary feasibility outcome measure to inform a future RCT sample size calculation, recommended feasibility trial sample sizes range between a total of 24 and 50 across two arms [56, 57].

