#### Secondary participant outcomes

At baseline and 9-week follow-up, the following will be measured using Amharic-translated scales. If scores are normally distributed, mean differences will be compared between arms using *t* tests and, if not normally distributed, median differences will be compared between arms using non-parametric statistical tests.

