### Statistical analysis

We will follow the Consolidated Standards of Reporting Trials (CONSORT) extension to randomised pilot and feasibility trials [83].

We will review process evaluation data for indications of sub-group differences in uptake, recruitment and retention of participants by site, health worker, recruitment method/site, participant (age, education level, religion, parity) and health worker characteristics (age, profession, years of experience). Quantitative scale results will be analysed using STATA [84].

Feasibility studies are not powered to calculate effect sizes but standard deviations and drop-out rates will be calculated on the intention-to-treat sample (all women who were randomised, regardless of uptake of the intervention) to inform sample size calculation for a future RCT, for outcome measures, recruitment rates and drop-out rates. Quantitative process data will determine future RCT design improvements, such as session number and duration, recruitment, outcome measures, and strategies preventing contamination. The extent of missing data will be evaluated as part of the process evaluation. For clinical outcome measures, missing data will not be imputed. Rather, standard deviations will be calculated using data from participants for whom outcome measures are available.

We will apply the framework approach to thematic analysis of qualitative interviews [85] and triangulate the results with quantitative process data through researcher meetings. The full descriptive analysis will include contextual barriers and facilitators influencing study outcomes.

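### PHQ-9 is compared as raw pre-post reduction and the secondary scales by unadjusted tests, although baseline scores are collected; the SD meant for the future RCT is not specified

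*Protocol article*

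**What the plan says.** Under Primary participant outcome: "At baseline and the independent, masked, 9-week follow-up interview, depression symptoms will be measured using the Amharic-translated PHQ-9". The contrast is then defined: "PHQ-9 scores pre- and post-participation will be compared to calculate the mean difference in depression symptom reduction" in the three arms. No test or model is named for it.

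Under Secondary participant outcomes, scales taken at the same two time points are handled by a distributional rule: "If scores are normally distributed, mean differences will be compared between arms using" t tests; otherwise medians are compared by non-parametric tests. The text does not say whether these differences are in 9-week scores or in change from baseline. Neither reading includes an adjustment for baseline.

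On design parameters, Participant sample size gives the aim: "To estimate the standard deviation of the primary feasibility outcome measure to inform a future RCT sample size calculation". Statistical analysis adds that, without imputation, "standard deviations will be calculated using data from participants for whom outcome measures are available". Neither place says whether this is the SD of the 9-week score, of change, or of the residual after adjustment. No section mentions the baseline to follow-up correlation.

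**The concern.** Each woman with a 9-week score also has a baseline score on the same scale, and the stated comparisons do not make the best use of it. Subtracting baseline fixes its coefficient at 1 whatever the data say. An unadjusted comparison of 9-week scores fixes it at 0. A regression on baseline estimates it.

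Two things are at stake. The between-arm estimates will be less precise, and more exposed to chance baseline differences, than they need be. The SD carried forward to the definitive trial may also not match the analysis that trial will use. The second matters more, because parameters for a future RCT are a stated objective of this study.

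**Working it through.** **Inputs from the article.** "With a total sample size of 75 (25 participants randomised to PST-IPV, 25 to PST and 25 to enhanced usual care"; an assumed drop-out of 30%; PHQ-9 and the secondary scales at baseline and 9 weeks. The article gives no SD, correlation or design effect, so there is no planned figure on this point to reproduce. Its one computed design figure, "a drop-out rate of 30% can be estimated to within a 95% confidence interval of ±3" percentage points, concerns drop-out. It does not reproduce (1.96 × √(0.3 × 0.7/75) = 10.4 points), but that is a separate matter and nothing below uses it.

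**Assumptions.** r = correlation of baseline with 9-week score; k = baseline SD / 9-week SD. Neither is in the article, so ranges are shown.

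**Variance per woman, in units of the 9-week variance**
- 9-week score alone: 1
- Change: 1 + k² − 2kr
- Baseline-adjusted (ANCOVA): 1 − r²
- Excess of change over ANCOVA: (1 + k² − 2kr) − (1 − r²) = (k − r)²

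The excess is never negative and is zero only at k = r. This is a large-sample result; estimating the slope costs one degree of freedom. Change is noisier than the 9-week score alone when r < k/2.

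**Ratio of change to ANCOVA variance**

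| r | k = 1, ratio 2/(1 + r) | k = 0.7 |
|---|---|---|
| 0.3 | 1.40/0.91 = 1.54 | 1.07/0.91 = 1.18 |
| 0.5 | 1.00/0.75 = 1.33 | 0.79/0.75 = 1.05 |
| 0.7 | 0.60/0.51 = 1.18 | k = r, so 1.00 |

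Entry requires a PHQ-9 score of 5 or more. That restriction tends to lower r, which raises the ratio, but it also tends to shrink the baseline SD, which lowers it. The equal-SD column should therefore not be read alone. If the secondary t tests are on 9-week scores only, their variance ratio to ANCOVA is 1/(1 − r²): 1.10, 1.33 and 1.96 at r = 0.3, 0.5 and 0.7.

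**Chance imbalance.** With 25 per arm, the standard error of a baseline difference between two arms is √(2/25) = 0.28 baseline SD. An imbalance of that size moves the change contrast by (k − r) × 0.28 of a 9-week SD, making the arm that started higher look as if it improved more when k > r. At k = 1 this is 0.20 (r = 0.3) or 0.14 (r = 0.5). At k = 0.7 it is 0.11 or 0.06.

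**Which SD.** For illustration only, take a difference of 0.34 9-week SDs (the meta-analytic PST effect cited in Background and rationale, not a design effect of this trial), two-sided 5% and 80% power. Per arm, n = 2 × (1.96 + 0.84)²/0.34² × variance ≈ 135.8 × variance, rounded up:

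| r | 9-week SD | change SD, k = 1 | change SD, k = 0.7 | residual SD |
|---|---|---|---|---|
| 0.3 | 136 | 191 | 146 | 124 |
| 0.5 | 136 | 136 | 108 | 102 |

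**Precision of the residual SD.** 75 × 0.7 = 52.5, so about 52 women. The model has four coefficients (intercept, two for arm, one for baseline), which leaves 48 df. The 95% limits are √(48/χ²) times the estimate, about 0.83 to 1.25.

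**The case against.** The strongest reply is that this is a feasibility trial, expressly not sized for efficacy, and that no decision rests on the between-arm comparisons. That stands: it limits the consequence and means adjusted differences should be presented as descriptive. It does not remove the point, because the comparisons will still be made and the variance parameters are a deliverable.

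A second reply is that the PHQ-9 sentence names no test, that a baseline-adjusted model of change gives the same arm effect as one of the 9-week score, and that covariates may be set out in a full protocol or analysis plan not shown here. This also has force: the wording does not forbid adjustment. But the contrast as written is raw reduction, and for the secondary scales unadjusted tests are actually specified. A later plan would have to replace that text, not just add to it.

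Four stronger readings are tempting and are not supported:
- **That the plan yields the wrong SD.** The article never says the SD of change will be used. A 9-week SD is a valid input and is conservative for an RCT analysed by ANCOVA.
- **That the RCT team could not recover the right figure.** Both scores exist for the same women, so the correlation can be computed, and Data Availability promises the minimum dataset behind the findings.
- **That PHQ-9 will be compared by t test.** That test is named only for secondary outcomes.
- **That the future RCT would be 18% to 54% too large.** That range needs equal SDs, and a change SD used unconverted to size an ANCOVA trial, which the article does not propose.

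**Conclusion.** The point holds as a modest and cost-free improvement to stated methods. The PHQ-9 contrast as worded, and the tests named for the secondary scales, leave the baseline score either crudely used or unused. The variance penalty of change against ANCOVA runs from 1.54 down to 1.18 for r from 0.3 to 0.7 if the two SDs are equal. It is only about 1.18 to 1.05 for r from 0.3 to 0.5 if the baseline SD is 0.7 of the 9-week SD, and vanishes where k = r. All of this rests on assumed r and k and on large-sample variances. The SD for the future RCT is unspecified; that creates a risk of a mismatch, not an established error.

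**What to change.** For each continuous scale, replace the raw-reduction contrast and the t test or non-parametric rule with one linear model: 9-week score on arm (three levels) plus baseline score, in all women with a 9-week score. Report adjusted differences with 95% confidence intervals, labelled as descriptive.

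In Participant sample size and Statistical analysis, say which variance parameters will be reported for RCT planning: baseline SD, 9-week SD, their correlation, and the residual SD pooled over the three arms with its 95% confidence interval. A future team can then size the trial for whichever analysis it chooses.

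The cost is a change of analysis wording. No extra participants, visits or measurements are needed.

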#### Secondary participant outcomes

At baseline and 9-week follow-up, the following will be measured using Amharic-translated scales. If scores are normally distributed, mean differences will be compared between arms using *t* tests and, if not normally distributed, median differences will be compared between arms using non-parametric statistical tests.
Post-traumatic stress symptoms using the PTSD checklist for the Diagnostic and Statistical Manual version 5 (PCL-5) [68] which has been adapted for a rural Ethiopian contextAnxiety symptoms using the Generalised Anxiety Disorder 7 (GAD-7) scale [69]Disability using the 12-item Ethiopian adaptation [70] of the WHO Disability Assessment Schedule (WHODAS 2.0) [71]IPV: participants will be asked about past-month IPV at baseline and 9-week follow-up to determine whether the frequency of different types of IPV (physical, sexual, psychological, coercive control) change during the study periodSelf-efficacy using an adapted self-efficacy scale validated in Ethiopia for sexual health research [72]Mastery (the extent to which the person considers themselves in control of forces affecting their lives in important ways [73]) using a 15-item multi-cultural mastery scale [74] adapted for rural, non-Western communitiesPerceived social support using the Oslo Social Support Scale 3 (OSSS-3) [75] previously used in this region in a study of antenatal depressive symptoms [46]Health care-seeking behaviour using the client service receipt inventory [76] adapted for Ethiopia [77] and modified to focus on the past month; the client service receipt inventory will be used to quantify the frequency of primary health care visits, inpatient admissions, private sector (including traditional healer) contacts, medications and investigations of women in each arm, in the past month, pre- and post-participationAdverse events or unanticipated harms taking place during the study periodObstetric and neonatal outcomes: HEWs, who maintain maternal care records, will report the location of birth and any stillbirths and early neonatal deaths among study participants, attendance at subsequent ANC appointments and medication prescriptions for physical and mental health, as they are not reliably self-reported [47]; where women attend ANC at a combination of HEW health posts, health centres and/or primary hospitals, antenatal contacts at all relevant services will be collected; the feasibility of collecting this data will be explored during analysisAttitudes towards gender roles using the WHO Attitudes Towards Gender Roles questionnaire [42]

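### Secondary scale scores are to be tested between three arms by a loosely defined t-test or non-parametric rule, in a trial that says it is sized for estimation and not for efficacy

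*Protocol article*

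**What the plan says.** The Secondary participant outcomes section sets one rule for scales measured at baseline and 9 weeks. "If scores are normally distributed, mean differences will be compared between arms using" t tests; "if not normally distributed, median differences will be compared between arms using non-parametric statistical tests". It states no significance level, no set of contrasts among the three arms and no exploratory label.

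Elsewhere the protocol gives the trial a different purpose:

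- Participant sample size: "this study is not powered to detect intervention efficacy, but rather to estimate feasibility parameters to inform a future RCT".
- Statistical analysis: "Feasibility studies are not powered to calculate effect sizes but standard deviations and drop-out rates will be calculated".
- Primary participant outcome: mean differences and response proportions on the PHQ-9 are planned, lack of power is acknowledged again, and no test is named.
- Objectives: the quantitative aim includes estimating parameters for the design of a future RCT.

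The allocation is "25 participants randomised to PST-IPV, 25 to PST and 25 to enhanced usual care". Missing clinical outcome data are not to be imputed.

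**The concern.** The protocol describes its primary clinical outcome without naming a test, yet prescribes between-arm tests for the secondary scales. These scales include hypothesised mediators such as mastery and self-efficacy, and the trial is meant to generate hypotheses about mechanism. With small arms and many comparisons, some p-values below 0.05 would be expected by chance, and most real differences of moderate size would be missed. Either result could be over-read when hypotheses and outcome measures for the full trial are discussed.

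The rule is also hard to carry out as written, for three reasons:

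- A two-sample t test compares two arms, and this trial has three.
- The usual rank tests ask whether values in one arm tend to exceed those in another. They compare medians only under added conditions, such as distributions that differ by a shift alone.
- The observed shape of the data decides whether a mean or a median difference is reported. One scale may yield a mean difference and the next a median difference, and neither need match what the future trial will estimate.

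**Working it through.** **The plan's own figure.** No power or significance level is given for these tests. The only numerical precision statement concerns drop-out: "a drop-out rate of 30% can be estimated to within a 95% confidence interval of ±3" percentage points. It does not reproduce: 1.96 × √(0.3 × 0.7 / 75) = 0.104, or about ±10 points. That is a separate matter, and nothing below depends on the ±3.

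**Inputs.**

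- 25 women per arm, from the sample size section.
- 30% drop-out, the rate used there. With no imputation this leaves 25 × 0.7 = 17.5 analysed per arm.
- Seven scored scales in the secondary list: PCL-5, GAD-7, WHODAS 2.0, self-efficacy, mastery, OSSS-3 and attitudes towards gender roles.
- Assumed, because not stated: two-sided 5% tests and all three pairwise contrasts.

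**Number of tests.** 7 × 3 = 21. If every null hypothesis is true, the expected number of false positives is 21 × 0.05 = 1.05. If past-month IPV were also scored, there would be 8 × 3 = 24 tests and 1.2 expected.

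The chance of at least one false positive would be 1 − 0.95^21 = 66% if the tests were independent. They are not, because contrasts share arms and scales are correlated. In a simulation with 25 per arm, it was 59% with uncorrelated scales and 39% with a correlation of 0.7 between scales.

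**Detectable difference at 80% power.** The normal approximation is (1.96 + 0.84) × √(2/n), in SD units. The noncentral t distribution gives slightly larger values.

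| n per arm | Normal approximation | Noncentral t |
|---|---|---|
| 25 | 0.79 | 0.81 |
| 17.5 | 0.95 | 0.98 |

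As an illustration, the background section cites a standardised effect of 0.34 for PST on depression. Power for a difference of that size is 22% with 25 per arm and 16% with 17.5. Reaching 80% would take about 2 × 2.80² / 0.34² = 136 per arm.

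**What the data-dependent choice does.** The protocol does not say how normality is judged. Taking a Shapiro-Wilk test at 5% in each of two arms of 25, followed by a t test or a Mann-Whitney test, simulation gave:

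- With truly normal scores, the t test was kept in 91% of comparisons, so about 9% moved to the rank test by chance.
- With moderately skewed (gamma or lognormal) scores, the t test was still kept in about 13%.
- The false-positive rate per comparison stayed at 4.5–5.1% throughout.

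The check therefore changes what is being compared. It does not change the error rate of each test.

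**Precision if estimates are reported instead.** The 95% half-width for an unadjusted pairwise difference is t × √(2/n): 2.01 × √(2/25) = 0.57 SD, or 2.03 × √(2/17.5) = 0.69 SD. Baseline adjustment would narrow this by a factor √(1 − r²), where r is the correlation between baseline and follow-up. The protocol does not give r.

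**The case against.** The strongest reply is that the protocol is candid. It says three times that power is lacking, commits to the CONSORT extension for pilot and feasibility trials, and lists standard deviations, drop-out rates, recruitment rates and process data as the inputs to the future trial. No passage makes progression, outcome choice or a conclusion on mechanism depend on these p-values. That stands: the harm is one of interpretation. The choice of contrasts and any multiplicity rule could also be left to an analysis plan. The fault is that the article already fixes a rule, and that rule pairs tests with quantities they do not address.

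Two stronger readings are tempting but are not supported:

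- A reader might infer that every listed item is to be tested, including adverse events, birth outcomes and service counts. The rule is worded for scores, and the protocol handles serious adverse events as numbers per arm and service use as frequencies. The sensible count is the seven scales.
- A reader might infer that choosing the test by a normality check itself produces false positives. The simulation above shows no such inflation. They come from the number of tests.

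Two further limits apply. The 0.34 effect is for depression, the primary outcome, so the 22% and 16% are illustrative for these scales. And a 95% interval that excludes zero is equivalent to a 5% test, so intervals alone do not remove multiplicity.

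**Conclusion.** The point holds for the secondary scale scores. The prescribed tests sit badly with the stated purpose and sample size, and the rule does not define a three-arm comparison or keep one estimand across scales. Its size is about one chance finding in 21 tests if no arm truly differs, and 80% power only for differences of roughly 0.8 to 1.0 SD. These figures rest on two-sided 5% tests, three pairwise contrasts and up to 30% loss per arm. The change should be made, but the matter is modest, because nothing in the protocol makes a decision turn on these results.

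**What to change.** Replace the t-test/non-parametric sentence with:

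> For each scored scale we report mean and SD by arm and the baseline-adjusted mean difference with 95% CI for each pair of arms (bootstrap CI if skewed), labelled exploratory; no hypothesis tests are done and no conclusion on efficacy or mechanism is drawn from whether a CI excludes zero.

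This keeps one estimand for every scale; skewness then alters only how the interval is computed. All three pairs of arms stay in view. The last clause is needed because intervals alone would let the same chance findings back in.

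The cost is small. Baseline scores are already collected, so no new data are needed, and the only loss is p-values the trial says it is not powered to support. Under the Trial status section the change would go to the two ethics boards and the registry. That section also says recruitment has not begun.

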## Methods

### Study setting

The study will be conducted in selected health facilities in the predominantly rural areas of Gurage zone (projected population 1,712,506) and Silt’e zone (projected population 1,043,242) in the Southern Nations, Nationalities, and Peoples’ Region of Ethiopia [51]. Primary health care is structured so that the nurse, midwife and health officer-run health centres (serving a population of 25,000–40,000) are linked to five community health posts (serving a population of 3000–5000) staffed by one or two health extension workers (HEWs) each, with access to a single primary hospital for more specialist care. HEWs, who have completed high school and received 1 year of undergraduate-level training [52], provide a first antenatal contact before referring women for further antenatal care (ANC) at a health centre or primary hospital and maintain contact with women during pregnancy.

This study builds on the programme for improving mental health care (PRIME) study [53], which integrated mental health into primary and maternal care in five LMICs, including the Gurage zone, Ethiopia [54]. In PRIME, a district-level mental health plan was developed in collaboration with key stakeholders and comprised interventions at the community, health facility and health system level. At the facility level, PRIME trained primary and maternal care staff using the mental health gap action programme (mhGAP) intervention guide of the WHO, which guides non-mental health specialists through clinical diagnostic and treatment algorithms for prioritised mental, neurological and substance use disorders [55]. The PRIME study investigators identified low detection rates of depression, which may be related in part to a lack of acceptable treatment options. Formative work was therefore conducted to inform adaptation of a brief psychological intervention for depression. In a nested study, PST was then adapted for antenatal women in this rural Ethiopian setting.

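### Birth outcomes sit under a 9-week time point that, unless most women enrol late, falls before most births; the protocol article should give them a birth-linked collection time

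*Protocol article*

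**What the plan says.** In the protocol article, Secondary participant outcomes opens with: "At baseline and 9-week follow-up, the following will be measured using Amharic-translated scales". The obstetric and neonatal item stands in that list: HEWs, as keepers of the maternal care records, "will report the location of birth and any stillbirths and early neonatal deaths among study participants". The same item also covers later antenatal attendance and prescriptions, and says that whether these data can be gathered is to be looked at during the analysis. It carries no time point of its own.

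Other places bear on the timing:

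- Participant eligibility criteria: entry at 12 to 34 weeks' gestation.
- Intervention arms: after the baseline assessment there are "four intervention contacts and a follow-up research assessment contact 9 weeks after recruitment".
- Enhanced usual care arm: a pre-intervention contact and "one follow-up assessment 9 weeks later".
- Intervention arms, on flexibility: "The feasibility of follow-up 9 weeks after recruitment will be assessed and may change, depending on gestation of pregnancy at the time of enrolment".
- Study setting: HEWs "maintain contact with women during pregnancy".
- Intervention arms, on early births: "Where birth occurs before the end of treatment, the feasibility of continuing PST-IPV or standard PST post-natally will also be assessed".

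Fig. 2, which gives the schedule of assessments, is not shown.

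**The concern.** The only time point in the visible text that covers the birth item is the 9-week follow-up. For a woman who enters in mid-pregnancy, that point comes well before birth. Location of birth, stillbirth and early neonatal death would then be missing for her, whatever the quality of the HEW records.

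Two things are at stake.

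- **Selection.** A woman enrolled before 28 weeks is short of 37 weeks at the 9-week point, so if she has delivered by then, the birth was preterm. The births on record would be a mix of late enrollers and preterm births. Stillbirth and early neonatal death rates among them would be a poor guide for the future trial, and estimating parameters for that trial is a stated objective.
- **The feasibility question itself.** The article wants to learn whether these data can be collected through HEWs. At 9 weeks, low completeness would mainly show that births had not yet happened. The HEW route would go largely untested.

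**Working it through.** The article gives no figure for the share of women delivered by follow-up, so there is nothing to reproduce.

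**Inputs from the article.** Enrolment at 12 to 34 weeks (Participant eligibility criteria); follow-up at 9 weeks (Secondary participant outcomes; Intervention arms; Enhanced usual care arm); 75 women, 25 per arm (Participant sample size).

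**Assumptions not in the article.** The spread of enrolment within the window; gestation at birth, B, of 37 to 42 weeks; early neonatal death taken as death in the first 7 days.

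**Step 1: gestation at follow-up.** 12 + 9 = 21 weeks to 34 + 9 = 43 weeks.

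**Step 2: who has delivered.** A woman has delivered by the 9-week point if she enrolled at B − 9 weeks or later. For B = 40, that is 31 weeks or later.

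**Step 3: share delivered, enrolment even over 12 to 34 weeks.** Share = (34 − (B − 9)) / 22. For a completed first week of life, replace B − 9 by B − 8.

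| Birth at week B | Delivered by week 9 | Of 75 | First week complete | Of 75 |
|---|---|---|---|---|
| 37 | 6/22 = 27.3% | 20.5 | 5/22 = 22.7% | 17.0 |
| 38 | 5/22 = 22.7% | 17.0 | 4/22 = 18.2% | 13.6 |
| 40 | 3/22 = 13.6% | 10.2 | 2/22 = 9.1% | 6.8 |
| 42 | 1/22 = 4.5% | 3.4 | 0/22 = 0% | 0 |

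At B = 40 this is 25 × 3/22 = 3.4 delivered women per arm.

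**Step 4: later enrolment.** If enrolment is even from week s to week 34, the share is (34 − (B − 9)) / (34 − s). For B = 40: s = 20 gives 3/14 = 21.4%; s = 24 gives 3/10 = 30%; s = 28 gives 3/6 = 50%.

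**Step 5: variable gestation at birth.** Simulation with normally distributed gestation at birth (mean 39 to 40 weeks, SD 1.5 to 2), leaving out births before enrolment:

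| Enrolment pattern | Delivered by week 9 | First week complete |
|---|---|---|
| Even, 12 to 34 weeks | 14% to 18% | 9% to 14% |
| Even, 20 to 34 weeks | 22% to 29% | 15% to 22% |
| Triangular, 12 to 34 weeks, peak at 34 | 25% to 32% | 18% to 25% |
| Even, 24 to 34 weeks | 30% to 40% | 21% to 31% |
| Even, 28 to 34 weeks | 50% to 64% | 34% to 50% |

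Only the last pattern brings the delivered share to half or more.

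**The case against.** The strongest reply is that the 9-week time point was never meant for this item. The lead-in speaks of translated scales, and the sentence after it compares scores. Place of birth and neonatal death are neither, and have no baseline value. Other items in the list carry timing of their own: adverse events over the study period, service use before and after participation, and IPV with the two time points restated. The source is also not the 9-week interview but HEW records, which can be read at any later date. The article says follow-up timing may shift with gestation, and it makes collection of these data an open question. The date may stand in Fig. 2 or in the supplementary data collection forms, neither of which is shown.

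Much of this stands. A reader might infer that the birth outcomes cannot be observed at all under the schedule. The documents do not support that: late enrollers will have delivered by week 9, and the records outlast the visit. Nor do they support the inference that most women will certainly be undelivered, since no enrolment distribution is given. A planned test between arms on birth outcomes should not be read in either, because the tests described are for scale scores. Antenatal attendance and prescriptions, in the same item, can be partly observed by week 9.

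What the reply does not do is supply a date. If the lead-in does not govern the item, the visible text gives it no collection time. The remark on changing the follow-up time has no rule and no link to birth. HEW contact is described for the pregnancy only, and birth during treatment is handled as a contingency. So this is more than condensed detail: the one time point that the text places over these outcomes does not fit them.

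**Conclusion.** The point holds in a limited form. Read as written, the three birth outcomes would be incomplete at 9 weeks, and selectively so, unless most women enrol late. With even enrolment and birth at 40 weeks, about 10 of 75 women would have delivered, and about 7 of 75 would have a newborn past its first week. The size depends on the assumed enrolment spread and gestation at birth. The direction holds for every pattern tried except enrolment almost wholly at 28 to 34 weeks, and even there no more than about half would have the first week complete.

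The item is secondary and descriptive and drives neither the sample size nor the primary outcome. This is a cheap improvement, held with moderate confidence because the schedule figure is not shown and may already give a time.

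**What to change.** If Fig. 2 or the full protocol already gives a birth-linked time, repeat it in the text. If not, for location of birth, stillbirth and early neonatal death only:

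- State that HEW or facility records are read once, at a fixed time after each woman's expected delivery date, in the same way in all three arms. Four weeks would do as an example: a birth at 42 weeks completes its first week at 43 weeks, before the reading at 40 + 4 = 44 weeks.
- Use all randomised women as the denominator, and report the proportion with a known birth outcome, by arm, as the feasibility result.
- Keep antenatal attendance and prescriptions at 9 weeks.
- Lock the 9-week data separately. The Risk of harm section ties the start of analysis and the end of the right to withdraw data to the final data collection, so say which collection is meant.

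The cost is small. No extra participant visit is needed. For a woman enrolled at 12 weeks, the reading falls 44 − 12 = 32 weeks after enrolment, which is 32 − 9 = 23 weeks after her 9-week assessment. For one enrolled at 34 weeks it falls 44 − 34 = 10 weeks after enrolment. The downside is a later lock for this one item.
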